### Infant developmental outcome

#### Perinatal data, neuromotor and cognition

We will collect a range of data on neonatal outcome, informed by existing evidence of neonatal deviations in muscle tone and neuromotor weakness in high risk infant [76–78] using *Neonatal Intensive Care Unit Network Neurobehavioral Scale* (NNNS) [41]

Routinely available data including Apgar score, birth weight, gestational age, and obstetric complications will be collected from the mothers, national registers and case notes.

Given the established literature on developmental delays in cognitive and motor domains (e.g. [79–81]. we will assess development milestones using The *Bayley’s Scales for Infant Development 3rd Edition* (BSID-III) [82]. The BSID III items fall into the developmental areas of cognition, language and motor skills.

#### Stress-sensitivity

Increased stress-sensitivity has been proposed as a risk factor for development of psychosis and other severe mental disorder [83]. Stress-sensitivity might be inherited [83], a result of exposures during the prenatal period [43] or a result of postnatal stress. It has been associated to maternal stress and quality of mother infant attachment relationship [47, 83]. Infants with insecure and disorganized attachment classification have elevated cortisol levels during separation in the Strange Situation Procedure [84]. Infants classified as disorganized in attachment show greatest elevation and slowest return to baseline cortisol levels after SSP [85, 86]. They also differ from non-disorganized infants in diurnal cortisol rhythm, displaying a more flattened daily curve [45].

*Stress-sensitivity* is measured by saliva cortisol sampling in relation to mild stressors. Cortisol concentration is measured in saliva samples three times across the study. Each time three saliva samples are collected i.e. before the stressor (baseline), 20 min after (reaction) and 40 min after the stressor (recovery). Stressors are the NNNS examination (4 weeks), the Still Face Procedure (16 weeks) and the SSP (52 weeks, see Table 1 and 2).

#### Attachment

Attachment is an important domain of child socio-emotional development and is predictor for later psychopathology [87, 88].

*Strange Situation Procedure* (SSP) [59] will be used to assess the infants attachment and socio-emotional development. SSP provides a measure of the infant’s attachment behavior according to the four ways classification system: secure, avoidant, ambivalent/resistant and disorganized. In this procedure the infant is videotaped in a playroom during a series of eight structured 3-min episodes involving the infant, the mother, and a female stranger.

Our review [35] found evidence of greater attachment insecurity in offspring of mothers with psychosis compared to normal controls and greater avoidance compared to offspring of mothers with depression. Infant attachment data from offspring of mothers diagnosed with schizophrenia were assessed in three studies [89–91]. All used the Strange Situation Procedure (SSP) [84] for assessing infant attachment, however two studies used an abbreviated procedure (using only three or four of the eight episodes in the SSP). The third study, which used the full SSP found the largest proportion of insecure attachment in the schizophrenia group [89]. Only two ways (secure, insecure) and three ways (avoidant, ambivalent/resistant, secure) assessment of attachment type was carried through, whereas the additional disorganized attachment type, most clearly associated with psychopathology, was not assessed in psychosis. There are indications of and high rates of insecure and disorganized infant attachment in offspring of mothers with depression [66] and in offspring of mothers with bipolar disorder [67–69].

### Procedure

The study has been approved by The committees of Health research Ethics in the Captial Region of Denmark (Protocol no: H-2-014-024) and by the West of Scotland Research Ethics Service and the NHS GG&C Board Approval (REC Reference 14/WS/1051). The project is registered with ClinicalTrial.Gov (https://clinicaltrials.gov/ct2/show/NCT02306551). The study launched in October 2014 and the recruitment period is expected to be 3–4 years. Participants in Denmark are recruited from Region Zealand and Region Southern Denmark and in Scotland from Greater Glasgow and Clyde. Potential participants are identified by obstetric consultants screening referrals to obstetric wards and by midwifes at midwiferies. In addition perinatal mental health services and community mental health teams are invited to approach and refer participants to the study. Women in Scotland can also self-refer. All mothers with probable inclusion diagnoses will be approached for their consent to be referred to the research team. All those who consent to be referred to the research project will be approached for their informed and written consent by the research team. The diagnoses are confirmed by the research team, which carry out baseline data collection as well as follow-ups. This team consists of three PhD students, a postdoc and an assistant professor. If an inclusion diagnosis cannot be confirmed, the participant will be excluded from the study. The numbers of mothers with depression or without a psychiatric history are more numerous in services. In order to guard against introducing selection biases we will randomly select which mothers from these groups that are referred to the study. Randomization lists will be constructed electronically and will determine the order in which mothers, identified within a specific month, are approached for referral to and consent into the study. Once we have reached the monthly limit on participants from the mothers with depression or without psychiatric history recruitment from these groups will stop for that month.

### Sampling, power and proposed data analyses

Sample size is set to *N* = 200, with 50 participants in each group (inclusive of Denmark and Scotland). With this sample size, we can detect an effect size of 0.24 between groups (small to medium effect size) with a 5 % level of significance (alpha) and a power of 80 %.

Basic characteristics of the cohort will be addressed using descriptive statistics (means and standard deviations for numeric variables and frequencies for categorical variables). Informed consent rate will be addressed by estimating the inclusion rate along with a 95 % confidence interval using the standard central limit theory based approximation. In order to investigate infant risk outcome, associated risk factors and transmission mechanisms we will employ mixed effects modelling to account for the longitudinal structure of the data and repeated sampling. The mixed effect model can also without any extensions handle missing outcome data and hence the proposed analytical approach is robust towards loss to follow-up. If missing variables at baseline, against our expectation, surpasses 5 % we will employ multiple imputations before conducting the analyses described above. Directed Acyclic Graphs [92] will be used to identify pathways from baseline variables (e.g. diagnosis) to infant outcome measurements and important confounders.

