### Participants

The study includes pregnant women with first or subsequent pregnancies at a minimum age of 16 (in Scotland) and 18 (in Denmark) and older who are willing and able to provide informed and written consent to participate, provide informed and written consent for their unborn infant to participate and who meet the following inclusion criteria: a) lifetime DSM-5 Delusional Disorder, Schizophreniform Disorder, Schizophrenia or Schizoaffective Disorder, Psychosis NOS, Brief Psychotic Disorder or b) lifetime DSM-5 Bipolar I and II Disorder or c) DSM-5 Major Depressive Disorder (current moderate or severe single episode or lifetime recurrent moderate or severe) or d) a non-psychiatric control group defined as mothers without any history of treatment or admission for a psychiatric disorder or drug or alcohol addiction. Mothers describing current psychiatric symptoms not previously identified or treated and who are likely to require treatment will not be included. Exclusion criteria are: a) Unable to speak English or Danish; these are excluded because of the requirement to complete assessments, b) Miscarriage, c) Maternal diagnosis of Autistic Spectrum Disorder, d) Alcohol or drug dependency being the primary diagnosis. In the event that the women lose capacity to consent during participation in the study, maternal and infant involvement will be suspended until capacity is regained. The study is aiming at a sample size of 200 with 50 in each group, distributed proportionally between Denmark and Scotland.

Partners will be approached for their informed consent and will be eligible if they are: a) the biological parent of the infant and have a caregiving role in relation to the infant or, b) partners who have a caregiving role in relation to the infant but are not the biological parent of the infant or; c) another person nominated by the mother who is in a close caregiving role (e.g. grandmother).

Infants will be included in the study from birth, if the parents (mother in Scotland) having parental responsibility for the child have provided informed and written consent for their child to participate in the study. There are no a priori exclusion criteria for the infant.

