### Assessments

The mapping of assessment domain to measurement is detailed in Table 1 and the schedule of measurements is illustrated in Table 2. All measures are validated.

**Table 1 Tab1:** Mapping of domains to measurements

Risk	Measure	Person
Diagnosis	SCID	Mother
Personality disorder screen	SAPAS	Parents
Predictors & moderators		
Symptom severity	MADRS	Mother
	BRMRS	Mother
	PANNS	Mother
	BSI-53	Father
Trauma	ACES	Mother
Attachment	AAP	Parents
	AAI	Mother
	Psychosis Attachment Measure	Parents
Parental alliance	Parental Alliance Measure	Parents
Father- infant interaction	Naturalistic play	Father-infant
	CIB	
	P-PATS (subscale)	
Social support	SOS	Parents
Socioeconomic status	Questionnaire	Parents
Demographics	Questionnaire	Parents
Cognition	RIST	Parents
Social functioning	GAF	Mother
Newborn characteristics	APGAR	
	NNNS	
Transmission mechanisms		
Stress-exposure	Parenting Stress Index Short Form	Mother
	Perceived Stress Scale	Mother
	Hair samples/	Mother & infant
	Mass spectrometry analysis	
Stress-sensitivity	Saliva samples/	Mother
	Mass spectrometry analysis	
Caregiving representation	PCEQ	Parents
	CEQ	Parents
Mother- infant interaction	Naturalistic play	Mother-infant
	Still face	
	CIB	
	AMBIANCE	
	ICEP	
Obstetric complications	National registers/case notes	Mother
Infant outcome	Measure	
Infant neuromotor and cognition	NNNS	
	Bayley	
Infant behavior	CIB	
Infant attachment	Strange Situation Procedure	
Stress-sensitivity	Saliva samples/	
	Mass spectrometry analysis	
Infant health	National registers/case notes

**Table 2 Tab2:** Schedule of assessments

Measure	Baseline	1–7 days	4 w	16 w	52 w
Mother					
Socio-demographics	X				
RIST	X				
SCID Lifetime mood and psychosis modules	X				
MADRS	X		X	X	X
BRMRS	X		X	X	X
PANSS	X		X	X	X
GAF	X	X	X	X	X
SAPAS	X				
AAP	X				
AAI	X				
SOS	X		X	X	X
Psychosis Attachment Measure	X				
ACES	X				
CEQ		X	X	X	X
PCEQ	X				
Cortisol Hair	X			X	X
Cortisol Saliva	X			X	X
Perceived Stress Scale	X			X	X
Parental Stress Index 3- Short Form				X	
Parental Alliance Measure				X	
Lifetimes diagnosis register/case notes					
Infant					
APGAR		X			
NNNS		X	X		
BSID_III-R				X	X
Cortisol Hair		X		X	X
Cortisol Saliva			X	X	X
Infant health from registers, case notes					X
Mother-infant interaction					
Naturalistic video interaction, CIB		X	X		
Still face/AMBIANCE/ICEP, CIB				X	
Strange Situation/AMBIANCE, CIB					X
Father					
RIST	X				
BSI-53	X			X	
AAP	X			X	
SOS	X				
PAM	X				
PCEQ	X				
CEQ		X	X	X	X
SAPAS	X				

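### The plan claims unconditional protection against dropout, but its mixed model needs missing at random and recovers nothing for attachment, which is measured once at 52 weeks

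*Protocol article*

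**What the plan says.** In the Protocol article, the section Sampling, power and proposed data analyses assigns one approach, mixed effects modelling, to infant outcomes, their risk factors and the transmission mechanisms. It says such a model needs no addition to cope with missing outcomes, and concludes: "hence the proposed analytical approach is robust towards loss to follow-up". It attaches no condition about why outcomes are missing. Multiple imputation is reserved for baseline variables, and only if more than 5% are missing.

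Four other places bear on this:

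- **Attachment (infant outcome).** The Strange Situation Procedure classifies infants "according to the four ways classification system: secure, avoidant, ambivalent/resistant and disorganized". In Table 2 the row "Strange Situation/AMBIANCE, CIB" is marked at 52 weeks only.
- **Participants.** The rule, quoted up to its last word, reads: "In the event that the women lose capacity to consent during participation in the study, maternal and infant involvement will be suspended until capacity is". Both may resume once the mother can consent again. Under Design, the postnatal visits are fixed by infant age.
- **Sample size.** The target is 200, split equally over four groups. The detectable difference is given as follows: "we can detect an effect size of 0.24 between groups (small to medium effect size"). Alpha is 5% and power is 80%. The passage mentions no allowance for loss.
- **Transmission mechanisms and Limitations.** The text on mother–infant interaction lists loss to follow-up among the biases of earlier cohorts. Limitations plans checks on recruitment and sampling bias, but none on loss after entry.

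**The concern.** The conclusion does not follow from the premise. That a mixed model runs with incomplete outcome data is a fact about computation. Whether its estimates are right depends on why the data are missing. The likelihood is valid if, given the observed data in the model, the chance of being missing does not depend on the unseen value, and if the model is correctly specified. The plan claims the result without the condition.

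The claim is weakest for attachment. A mixed model protects against dropout by using an infant's earlier values of the same outcome. Attachment has no earlier value, so an infant who misses the 52-week visit adds nothing to that analysis.

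At stake is how the results are read. If infants of mothers who become unwell are lost more often, contrasts between diagnostic groups and controls could be distorted, and the plan would report the problem as already solved.

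**Working it through.** **1. The plan's own figure.** Inputs: N = 200, four groups, alpha 5%, effect size 0.24 (type not named). Read as Cohen's f in a one-way analysis of variance, the noncentrality is N × f² = 200 × 0.24² = 11.52, with 3 and 196 degrees of freedom. Power is 0.815, and f for exactly 80% power is 0.236. The stated figure therefore reproduces with all 200 analysed.

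For a continuous outcome measured once at 52 weeks (only a guide for a four-category class), power at f = 0.24 falls with loss even if the loss is random:

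| Loss (assumed) | N analysed | Power | f detectable at 80% |
|---|---|---|---|
| 10% | 180 | 0.767 | 0.249 |
| 20% | 160 | 0.711 | 0.264 |
| 30% | 140 | 0.644 | 0.283 |

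**2. What the mixed model does for a repeated outcome.** This is a simulation with assumed inputs: 150 infants of ill mothers and 50 controls, visits at 16 and 52 weeks, correlation 0.5, true differences -0.25 SD and -0.50 SD. Controls are retained at 90%. The estimate is the 52-week difference from the two-visit normal likelihood.

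| Dropout in the ill group | Retained | Likelihood estimate | Completers only |
|---|---|---|---|
| Unrelated to outcome | 70.1% | -0.504 | -0.504 |
| Depends on the observed 16-week value | 65.1% | -0.505 | -0.341 |
| Depends on the unseen 52-week value | 66.9% | -0.254 | -0.184 |

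The second row shows the real benefit of the model. The third shows its limit: about half the difference is lost.

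**3. Attachment, measured once.** With true insecure proportion p and retention r₁ (insecure) and r₂ (secure), the observed proportion is p·r₁ / [p·r₁ + (1 − p)·r₂]. Take p = 0.60 (assumed):

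- r₁ = r₂ = 0.80: 0.48/0.80 = 60.0%
- r₁ = 0.70, r₂ = 0.90: 0.42/0.78 = 53.8%
- r₁ = 0.60, r₂ = 0.90: 0.36/0.72 = 50.0%

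**4. Why earlier maternal measures help.** Suppose (assumed) that 40% of a clinical group have a recorded maternal state that carries a 50% risk of disorganised attachment, against 20% in the rest. The true risk is 0.4 × 0.5 + 0.6 × 0.2 = 32.0%.

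- Loss of 40% v 10%: observed (0.24 × 0.5 + 0.54 × 0.2)/0.78 = 29.2%.
- Loss of 60% v 10%: observed (0.16 × 0.5 + 0.54 × 0.2)/0.70 = 26.9%.

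Within each state the observed risk is still right: at the first loss rates, 0.12/0.24 = 50% and 0.108/0.54 = 20%. Only the unadjusted group rate moves, and using the recorded state brings back 32.0%. Loss that depends on something measured can be repaired if that measurement is used. Loss that depends on the unseen outcome, as in step 3, cannot.

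**The case against.** The best defence is that this is a condensed article describing a general approach. It does not say that a repeated-measures model will be fitted to attachment class, and the choice of logistic or multinomial regression belongs in an analysis plan that is not shown. The aims are to identify and explore, with no confirmatory hypothesis. Mixed models do suit the infant outcomes that are truly repeated: coded interactive behaviour at all four postnatal visits and saliva cortisol at three. All of this stands and lowers the weight of the point. It does not rescue the sentence, which asserts a property that the method lacks.

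Three stronger readings are tempting and not supported:

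- **That loss is tied to maternal relapse.** The documents never mention relapse. The capacity rule is narrower, suspension may be temporary, and loss can have other causes. The rule is a reason to doubt missing at random, not proof that it fails.
- **That neuromotor and cognitive outcomes are unprotected because the instrument changes, leaving two values for each.** Two visits are enough, as the second row of the simulation shows.
- **That maternal severity would be left out of the models.** Design lists severity and course of illness among predictors and moderators, and the analysis section covers associated risk factors. Severity will probably enter at least some models, which makes missing at random more plausible without guaranteeing it.

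The illustrations also rest on assumed inputs. The shifts in step 4, 2.8 and 5.1 points, are smaller than one standard error for a single group (about 7.3 points at n = 39 and 7.5 at n = 35).

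**Conclusion.** The sentence is wrong as written and should be corrected. It is a limited, cheaply repaired fault and does not undermine the design. Two parts hold without any assumed figure: validity depends on missing at random given the modelled data, and the stated approach recovers nothing for attachment in infants not seen at 52 weeks. Covariates could still make an analysis of the infants seen valid, and a joint model or outcome imputation could draw on other data, but the article says neither that validity depends on this nor that missing outcomes will be imputed.

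That missing at random may fail is an inference from the capacity rule. The size of any bias cannot be fixed from the documents. The results above (-0.25 for a true -0.50 SD, and 50.0% to 53.8% for a true 60%) show what selective loss could do under the stated assumptions. They do not estimate what will happen in this cohort.

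**What to change.** 1. Replace the robustness sentence with a statement that the analysis is valid under missing at random given the variables used, and name those variables.
2. Analyse 52-week attachment by logistic regression (disorganised or not; secure or insecure) or multinomial regression. Impute missing classes within diagnostic group, using maternal MADRS, BRMRS, PANSS, GAF and SOS from the preceding visits at which Table 2 schedules them: baseline, 4 and 16 weeks, with GAF also at 1–7 days. Because suspension covers the mother too, her scores may be absent at the missed visit, so the earlier ones carry the information.
3. Add a delta-adjusted missing-not-at-random sensitivity analysis that makes imputed outcomes progressively worse over a range fixed in advance, and report how far the group contrasts change.
4. Report retention by group and by reason, with suspension for loss of capacity shown separately.

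The cost is a change of wording and some extra analysis of data already scheduled. Intervals may be slightly wider.

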### Paternal/significant other predictors and moderators

There is an increasing body of literature highlighting the impact both of paternal behavior on offspring development, and the contribution of the father’s mental state and availability to moderate the impact of maternal illness on the infant’s development and wellbeing [9, 39]. We have therefore included a short battery of measures for measuring paternal/significant other characteristics at baseline and follow-up (see Table 1 and 2 for measures applied). We have opted to leave the definition of significant other relatively broad to reflect contemporary social structures, including but not limited to fathers and kinship carers.

*Brief Symptom Inventory (BSI-53)* [40] is used to assess symptom level in the partner. It is a 53-item self-report inventory in which participants rate the extent to which they have been bothered in the past week by various symptoms.

Fathers and/ or significant others will also be invited to participate in a video recording while playing with the infant. The video recorded will last a period of 10 min.

*The Paternal-Physicality Affect and Touch Scale(PPAT),* subscale for excitatory arousal (Sethna, Murray and Ramchandani, 2008, Unpublished manual) is applied on video recordings of naturalistic father-infant play to assess paternal behavior.

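### The missing-data rules leave post-baseline mechanisms uncovered when they are used as predictors, so the claim of robustness to loss to follow-up goes too far; the 5% baseline trigger is also undefined

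*Protocol article*

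**What the plan says.** The section on sampling, power and proposed data analyses fixes two rules.

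- **Outcomes.** "The mixed effect model can also without any extensions handle missing outcome data and hence the proposed analytical approach is robust towards loss to follow-up".
- **Baseline variables.** "If missing variables at baseline, against our expectation, surpasses 5 % we will employ multiple imputations before conducting the analyses described above".

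The model's scope is wide: "In order to investigate infant risk outcome, associated risk factors and transmission mechanisms we will employ mixed effects modelling". The second objective is to explore how risk passes from parent to infant through stress, caregiving representation and mother-infant interaction.

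On partners, the Participants section says "Partners will be approached for their informed consent and will be eligible if they are" one of three kinds of caregiver, including a person nominated by the mother. The section on paternal and significant-other predictors says "We have therefore included a short battery of measures for measuring paternal/significant other characteristics at baseline and follow-up".

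**The concern.** A likelihood-based mixed model uses every observed outcome and is valid under missing at random. It has no corresponding device for a missing value on the predictor side. The imputation rule covers predictors, but only those measured at baseline. A predictor measured after baseline falls between the two rules, and most of the mechanism measures are of that kind.

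What is at stake is the mechanism analysis. A dyad whose infant outcome was observed is discarded because a mechanism score is missing. That always costs precision. It also biases the estimate if missingness is related to the outcome given the predictors in the model. The Participants section creates gaps linked to maternal illness: involvement is suspended when a mother loses capacity to consent, and resumes when she regains it. The dropped records may therefore come more often from the most severely ill mothers.

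Two weaknesses in the baseline rule add to this. The 5% is not said to be a share per variable, per woman or overall, and nothing is said about incomplete covariates at or below it. The expectation of staying under 5% also sits badly with partner data that depend on a second person's consent.

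**Working it through.** **1. Which rule covers which variable (Tables 1 and 2).**

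| Variable | When measured | As modelled response | As predictor or mediator |
|---|---|---|---|
| CEQ | 1–7 days, 4, 16, 52 weeks | mixed model | neither rule |
| Parenting Stress Index | 16 weeks only | mixed model | neither rule |
| CIB / AMBIANCE / ICEP | CIB from 1–7 days to 52 weeks; AMBIANCE 16 and 52 weeks; ICEP 16 weeks | mixed model | neither rule |
| Maternal hair and saliva cortisol, Perceived Stress Scale | baseline, 16, 52 weeks | mixed model | baseline value: imputation if above 5%; later values: neither rule |
| MADRS, BRMRS, PANSS | baseline, 4, 16, 52 weeks | mixed model | baseline value: imputation if above 5%; later values: neither rule |
| PCEQ | baseline | – | imputation if above 5% |

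Example: infant attachment is assessed once, at 52 weeks, and the Parenting Stress Index once, at 16 weeks. A dyad that misses week 16 and returns for week 52 has an observed outcome. It still leaves a model that uses parenting stress to predict attachment.

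**2. The plan's own power figure.** Inputs: "The study is aiming at a sample size of 200 with 50 in each group"; "we can detect an effect size of 0.24 between groups"; "with a 5 % level of significance (alpha) and a power of 80" per cent. I read 0.24 as Cohen's f in a one-way, four-group F test, with noncentrality N·f² and degrees of freedom 3 and N − 4. At N = 200 and f = 0.24 the power is 81.5%, and f = 0.236 is detectable at 80%. The stated figure reproduces. At f = 0.24, 80% power needs N = 194, so the margin is 6 women. (Read as a pairwise standardised difference at 50 against 50, power would be only 22.4%.)

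**3. Complete-case loss at or below the trigger.** The document gives neither a missingness rate nor a number of covariates, so both are assumptions. With k covariates, each missing in a share m independently, N = 200 × (1 − m)^k. If all gaps fall in the same women, N = 200 × (1 − m) for any k.

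| Assumption | N | Power at f = 0.24 | Detectable f |
|---|---|---|---|
| m = 5%, full overlap, or 5% caps women with any gap | 200 × 0.95 = 190 | 79.2% | 0.242 |
| m = 2%, k = 5, independent | 200 × 0.98⁵ = 180.8 | 77.0% | 0.248 |
| m = 2%, k = 10, independent | 200 × 0.98¹⁰ = 163.4 | 72.1% | 0.261 |
| m = 5%, k = 5, independent | 200 × 0.95⁵ = 154.8 | 69.4% | 0.269 |
| m = 5%, k = 10, independent | 200 × 0.95¹⁰ = 119.7 | 56.7% | 0.307 |

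These figures put the loss on the plan's own scale. They are not the power of an adjusted model, in which covariates may also reduce residual variance.

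**4. Partner measures.** Table 2 marks seven at baseline for the father: RIST, BSI-53, AAP, SOS, PAM, PCEQ and SAPAS. Ten mothers without an enrolled partner or caregiver is 10/200 = 5.0%, which does not exceed the limit; eleven is 11/200 = 5.5%, which puts all seven over it. No participation rate is given. If partner covariates are used with complete cases, assumed participation of 90%, 80% or 60% leaves N = 180, 160 or 120, with power 76.7%, 71.1% or 56.8%. The same arithmetic applies to any single predictor missing in 10%, 20% or 40% of women, including a mechanism measured once.

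**The case against.** The strongest case on the other side has four parts.

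- **Mechanisms are partly covered.** Where a mechanism is the modelled response, the mixed model handles its missing values, and several mechanisms also have a baseline value. This stands. The gap is confined to post-baseline mechanisms and symptom scores used as predictors or mediators.
- **Deletion is inferred.** A reader might conclude that the plan prescribes listwise deletion and will lose about a third of the cohort: ten covariates at 4% give 1 − 0.96¹⁰ = 33.5%, or 200 to about 133. The document does not support that. It names no deletion rule, does not say that ten covariates enter one model (Directed Acyclic Graphs are to identify the confounders), and does not make the 5% a per-variable figure. Baseline gaps may also cluster in the same women. The stated 0.24 reproduces as an unadjusted four-group comparison, which needs only group membership.
- **Partners would not necessarily be imputed.** A reader might infer that the rule would invent data for partners who do not exist. The text does not list the variables to be imputed, gives no participation rate, and lets a nominated caregiver fill the role. All that can be said is that partner measures are not excluded from the rule.
- **An article condenses a fuller plan.** This is fair for the details of the imputation model. It does not answer a robustness claim and a trigger that are both stated here and fixed badly.

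**Conclusion.** The concern holds in a limited form. The claim of robustness to loss to follow-up is supported for missing outcomes under missing at random, including mechanisms when they are the response. It is not supported when post-baseline mechanisms or symptom scores predict infant outcome. Those missing values fall under neither rule, and by default the records would drop out. The size of that loss cannot be computed, because no rate of missed visits is given. That it would fall more on the illest mothers is plausible from the suspension rule but not shown.

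The baseline trigger lacks a denominator and a method at or below it. Under complete cases the illustrative range is N about 190 (79% power) to about 120 (57%). The upper end needs full overlap or a per-woman cap; the lower end needs ten covariates, each 5% missing independently. The partner measures could cross 5% with 11 unpartnered or non-participating families, which makes the stated expectation doubtful but does not prove a breach.

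**What to change.** - **Replace the 5% trigger.** Use multiple imputation, whatever the rate, for incomplete baseline covariates and for post-baseline mechanisms and symptom scores used as predictors. Put infant outcome, diagnosis, country and visit in the imputation model.
- **Narrow the robustness sentence** to missing outcomes under missing at random. Imputation rests on a similar assumption, so it should not be presented as removing the problem.
- **Separate two kinds of absent partner data.** Where no partner or caregiver exists, treat the absence as structural: do not impute, and fit partner-moderator models in families with an enrolled partner. A partner who exists but declined is ordinary missing data, and its handling should be stated separately.

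The cost is revised plan wording and modest extra analysis work. No new data are needed.
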